**Methods:**

In this cluster-randomized controlled trial, CHSs will be randomly assigned to one of three implementation conditions: (1) Usual Implementation (UI), which consists of training workshops and toolkits; (2) Enhanced Supervision (ES), which includes UI combined with bi-weekly/monthly supervision; and (3) Community-Engaged Learning Collaborative (CELC), which includes all components of ES, combined with bi-monthly province-wide learning collaborative meetings, during which cross-site learning and continuous quality improvement (QI) strategies are implemented to achieve better implementation outcomes. The primary outcome will be measured based on the RE-AIM framework (Reach, Effectiveness, Adoption, Implementation quality, and Maintenance) using indicators on implementation, provider, and client factors. The secondary outcome examines factors associated with barriers and facilitators of quality implementation, while the tertiary outcome evaluates the incremental cost-effectiveness ratio of services provided in the ES and CELC conditions, relative to UI condition for depression care. A total of 1,296 clients receiving depression care at CHSs will be surveyed at baseline and 6-month follow-up to assess mental health and psychosocial outcomes (e.g., depression and anxiety severity, health function, quality of life). Additionally, 180 CHS staff and 180 non-CHS staff will complete pre- and post-training evaluation and surveys at baseline, 6, 12, and 24 months.

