### Outcome evaluation and analysis for AIM 1 (Fidelity to MCCD)

#### Power analysis

We used the pwr package in R software to determine the sample size and estimate power to detect a small eta-squared effect size of 0.025 with an expected intra-class correlation coefficient (ICC) of 0.2. Our primary outcome analyses focus on the 12-month timepoint, we will enroll 10 providers per site resulting a total of 360 providers (180 CHS staff and 180 non-CHS staff) across 36 sites in order to achieve 80% power to detect the small effect size. We also enroll 18 clients per site per phase which results in a total of 648 clients over two phases. With client outcome, power calculations assume near-normal outcomes with a two-sided Type I error of 0.05, this design has 80% power to detect small effects (small Cohen’s d effect size of 0.14 for a 3 × 3 contingency table chi-square test, given 4 degrees of freedom [(3 intervention groups {UI, UI + ES, UI + ES + CELC} − 1)*(3 outcome levels of PHQ-9 score change from baseline to 6 months {positive change, no change, negative change} − 1)]).

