#### Client outcomes

Clients identified with depression as part of routine depression screening at CHS will be recruited to participate in the client outcomes survey study across two implementation support phases. Eligible clients included those who are (1) new to the program, (2) aged 18–65, and (3) screened positive for depression using the PHQ-9 (score > 9). Those with a risk for severe mental illness (psychosis, mania, and substance abuse) will be excluded from the Client Study Cohort and referred to the provincial psychiatric hospital, per the stepped care model mentioned in the intervention description. Based on a depression screening rate of 20% and a research acceptance rate of 75% from our prior work [20], we expect CHS staff to screen 2,200 clients to consent 324 participants across each province for each Client Study Cohort. Across the total sample of 648 clients in each implementation phase. We will request permission from participants to link survey data to client administrative and clinical data.

The effectiveness on the client outcome will be measured based on the client’s improvement (defined as a 50% reduction in PHQ-9 score between the first and last BA session) and client’s remission (defined as the last PHQ-9 score less than 5). We will conduct an intent-to-treat analysis (e.g., those who are lost to follow-up are considered neither improved nor remised) in order to ensure the randomization process. A generalized linear mixed-effects model will be used for binary outcomes with a binominal family distribution and logit link. Exponentiating the fix-effect coefficients for treatment conditions will result in estimates of the odds ratio regarding the effect of treatment condition on depression symptomatology. These models will be adjusted for the clustering effects across multiple levels of hierarchical data structure (e.g., providers, clients) and the UI intervention will be used as a reference group.

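### The client-level 80% power makes no allowance for clustering within health stations, names the wrong effect index, misstates the client total, and is for an outcome and test other than those planned

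*Protocol article*

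**What the plan says.** All references are to the protocol article.

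The Power analysis section (under the Aim 1 evaluation) opens with an eta-squared effect of 0.025 and an expected ICC of 0.2, and goes on to the provider sample of 10 per site. For clients it says: "We also enroll 18 clients per site per phase which results in a total of 648 clients over two phases". It then says that "power calculations assume near-normal outcomes with a two-sided Type I error of 0.05" and that "this design has 80% power to detect small effects". The small effect is given as a Cohen's "d effect size of 0.14 for a" 3 x 3 "contingency table chi-square test, given 4 degrees of freedom". The rows are the three arms. The columns are better, unchanged or worse PHQ-9 from baseline to 6 months. No ICC or design effect is given for clients.

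Other sections describe the client sample and analysis differently. The Methods part of the abstract says: "A total of 1,296 clients receiving depression care at CHSs will be surveyed at baseline and 6-month follow-up". The Client outcomes section expects 324 consenting clients per province for each cohort and says: "Across the total sample of 648 clients in each implementation phase". Its planned endpoints are a 50% fall in PHQ-9 from the first to the last therapy session, and remission (last PHQ-9 below 5). For these, "A generalized linear mixed-effects model will be used for binary outcomes", with a logit link and an adjustment for clustering.

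**The concern.** The trial randomises stations, each contributing 18 clients per phase, and the planned client model allows for that. A power figure for this design needs an allowance for correlation between clients of the same station. The client statement mentions none, and the only ICC in the article is attached to a different calculation.

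Three further points concern the same statement. A contingency-table chi-square takes Cohen's w, not d, and a near-normal outcome does not describe a three-category table. The client total disagrees with the other sections by a factor of two. The outcome, time window and test that were powered are not those to be analysed.

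Effectiveness on clients is one of the RE-AIM components of the primary outcome. If the arms do not differ on it, readers will judge that result against a stated 80% power for a small effect, so the figure should belong to the design.

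**Working it through.** **Inputs.** From Power analysis: two-sided alpha 0.05, 4 df, effect size 0.14, 18 clients per site per phase. From Study site eligibility and recruitment: 36 stations, and two phases defined as active and then sustainable support. The client ICC is not stated, so values from 0.01 to 0.20 are assumed. The top value is the ICC given ahead of the provider sample size, assumed here to carry over to clients.

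**Step 1: client total.** 18 x 36 = 648 per phase, and 648 x 2 = 1,296 over two phases. The provincial figure agrees: 324 x 2 = 648 per cohort. The phases are periods of support, not provinces, so reading phase as province does not rescue a total of 648 over two phases.

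**Step 2: reproduce the stated power.** For a chi-square test the noncentrality is lambda = N x w². With 4 df and alpha 0.05, 80% power needs lambda = 11.935.

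- N = 648: detectable w = sqrt(11.935/648) = 0.136, which rounds to 0.14. At exactly w = 0.14 the power is 82.7%, and 80% needs N = 11.935/0.14² = 609.
- N = 1,296: detectable w = sqrt(11.935/1,296) = 0.096, and power at w = 0.14 is 99.0%.

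The stated figure therefore matches 648 independent clients with 0.14 read as w. No design effect is left in it, and the N used is the total for one phase.

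**Step 3: add clustering.** Design effect DE = 1 + (m - 1) x ICC, effective N = N/DE, then the same noncentral chi-square at w = 0.14. One phase has m = 18 and N = 648. Both phases pooled have m = 36 and N = 1,296. For example, at ICC 0.20 in one phase, DE = 1 + 17 x 0.20 = 4.4 and effective N = 648/4.4 = 147.3.

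| Assumed client ICC | One phase: effective N | Power | w at 80% | Pooled: effective N | Power | w at 80% |
|---|---|---|---|---|---|---|
| 0.01 | 553.8 | 76% | 0.147 | 960.0 | 95% | 0.112 |
| 0.02 | 483.6 | 69% | 0.157 | 762.4 | 89% | 0.125 |
| 0.05 | 350.3 | 53% | 0.185 | 471.3 | 68% | 0.159 |
| 0.10 | 240.0 | 37% | 0.223 | 288.0 | 44% | 0.204 |
| 0.20 | 147.3 | 24% | 0.285 | 162.0 | 26% | 0.271 |

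**Step 4: break-even ICC for 80% at w = 0.14.** Set effective N equal to 609.

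- One phase: (648/609 - 1)/17 = 0.004.
- Pooled: (1,296/609 - 1)/35 = 0.032.

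As the number of clients per site grows, effective N approaches but cannot exceed 36/ICC. At ICC 0.20 that ceiling is 180, below the 609 needed, so recruiting more clients per station could not restore 80% at that ICC.

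**Step 5: powered analysis beside planned analysis.**

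| | Power analysis | Client outcomes |
|---|---|---|
| Outcome | three-level PHQ-9 change | binary 50% improvement; binary remission |
| Window | baseline to 6 months | first to last therapy session; last score |
| Test | 4-df chi-square, no clustering | logit mixed model with clustering |

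**The case against.** **The ICC of 0.2 is not a client ICC.** It leads into the provider sample, and correlation between providers' survey answers need not equal correlation between clients' PHQ-9 changes. This stands. A reader might infer that the plan's own ICC implies 24% power, but the article does not support that. The 24% is one end of a range and rests on an assumption.

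**Pooling the phases may preserve the power.** The article does not say that client outcomes are analysed phase by phase. With all 1,296 clients, power at w = 0.14 is 95% at ICC 0.01 and 89% at 0.02. This also stands, so the break-even ICC of 0.004 must not be quoted without saying that it is for one phase. It does not rescue the statement as written, because the stated figure was computed on 648 clients without clustering.

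**The intended client total can be recovered.** The abstract, the Client outcomes section and 18 x 36 all point to 1,296. The Trial status section, with 324 clients interviewed in phase 1 and 18 stations recruited, fits 18 per station. This stands: the phrase is a slip, and it does not leave the target unknown.

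**Powering on a simpler test is common.** Table 1 lists pre- to post-treatment differences and PHQ-9 survey data under Effectiveness, so PHQ-9 change to 6 months is not foreign to the plan. This stands in part. The issue is a mismatch between the powered and the planned analysis, not an invalid test.

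**Condensation.** An article may leave the client ICC to a fuller document. That would explain a missing input, but not a stated 80% that matches independent observations.

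**Conclusion.** The concern holds as a fault of the power statement. The client-level 80% is an independent-observations figure, and reproducing it shows this without assuming any ICC. What it becomes after clustering depends on a client ICC that the article does not give and on whether phases are pooled. At w = 0.14 and ICCs from 0.01 to 0.20, power runs from 76% down to 24% for one phase and from 95% down to 26% pooled. It stays at 80% or more only up to an ICC of about 0.004 (one phase) or 0.032 (pooled). These figures assume equal numbers per station and no loss to follow-up, and they apply a simple design effect to the chi-square that the article used. They do not give the power of the planned mixed model.

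Two further errors need no assumption. The index is w, and 648 is the total per phase, with 1,296 over two phases. The mismatch between powered and planned outcome is also plain from the text.

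A reader might go further and infer that the client analysis itself ignores clustering. It does not: the Client outcomes section adjusts for it.

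**What to change.** In the Power analysis section:

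1. Change the client total to 648 per phase (18 x 36) and 1,296 over two phases.
2. Call the effect index Cohen's w if a chi-square calculation is kept, and remove the near-normal assumption from it.
3. State whether the client comparison is made per phase or pooled over phases.
4. Replace the 80% claim with power, or the detectable difference in response rate, for binary improvement and remission in the logit mixed model. Apply a design effect over a stated range of assumed client ICCs, for example 0.01 to 0.20, and give the reason for the range.

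Points 1 and 2 are wording. Point 3 needs a decision, and point 4 needs a justified ICC range and a short recalculation. No extra clients are needed and the planned analysis is unchanged. The cost is a stated power that will look less favourable.

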#### RE-AIM outcomes

According to the RE-AIM framework, for an intervention to have an impact, it must **Reach** the population in need of the service, demonstrate **Effectiveness**, be **Adopted** by the system and providers, be **Implemented** with quality, and be **Maintained** or sustained over time. The indicators’ description as well as data sources were presented in detail in Table 1. A cascade of MH care will be built based on these indicators (Fig. 2). Mean and standard deviation will be presented without the normality violation, otherwise, median and interquartile ranges will be used. Independent ANOVA and/or Kruskal-Wallis test will be applied to assess differences stratified by intervention arms.

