**Discussion:**

We hypothesize that the additional implementation supports will make mental health service implementation superior in the ES and CELC arms compared to the UI arm. The findings of this project could identify effective implementation models and assess the added value of specific QI strategies for implementing depression care in primary care settings in Vietnam, with implications and recommendations for other low- and middle-income settings. More importantly, this study will provide evidence for key stakeholders and policymakers to consider policies that disseminate, scale up, and advance quality mental health care in Vietnam.

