## Methods

### Study design

This Type-II Hybrid Implementation-Effectiveness study [40] will primarily test implementation strategies on provider adoption and implementation quality. We will use a cluster RCT design to test the effectiveness of the implementation models on provider- and client-level outcomes with a mixed-methods approach. Specifically, this three-arm trial compares the three multi-component strategies for implementing depression care guidelines: (1) UI arm which includes basic depression care capacity workshops, limited technical assistance, and toolkits, 2) ES arm which includes all components of UI and additional structured clinical supervision from provincial and district supervisors, and 3) CELC arm which includes all components of ES, combined with the activation of a community-wide network of providers and stakeholders who are implementing continuous QI strategies (Fig. 1). The primary outcome is to compare the fidelity of MCCD on three implementation models using the RE-AIM framework [41], which will be assessed based on implementation outcomes (**R**each, **A**doption, **I**mplementation quality, and **M**aintenance) and provider and client-related outcomes (**E**ffectiveness) (Table 1). The secondary outcome is to assess factors associated with barriers and facilitators of quality implementation, which may serve as mechanisms for implementing additional supports for the ES and CELC arms. The tertiary outcome is to evaluate the incremental cost-effectiveness which quantifies the cost savings to policymakers when integrating various strategies for task-shifting depression care into primary care settings.

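### For Reach, Adoption, Implementation Quality and Maintenance, the stated three-arm omnibus test does not test the stated hypothesis that ES and CELC are each superior to UI

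*Protocol article*

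**What the plan says.** The Discussion part of the Abstract sets out the expectation: "We hypothesize that the additional implementation supports will make mental health service implementation superior in the ES and CELC arms compared to the UI arm".

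In the Methods part of the Abstract, RE-AIM is made the primary outcome ("The primary outcome will be measured based on the RE-AIM framework"). The Study design section repeats this ("The primary outcome is to compare the fidelity of MCCD on three implementation models using the RE-AIM framework") and says that the trial mainly tests the strategies on provider adoption and implementation quality.

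Under Aim 1, the RE-AIM outcomes section gives one inferential statement for these indicators: "Independent ANOVA and/or Kruskal-Wallis test will be applied to assess differences stratified by intervention arms". The same paragraph commits to reporting means with standard deviations, or medians with interquartile ranges.

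The Client outcomes section treats Effectiveness differently. For improvement and remission it says: "A generalized linear mixed-effects model will be used for binary outcomes with a binominal family distribution and logit link". Clustering is adjusted for, "the UI intervention will be used as a reference group", and an odds ratio is obtained for treatment condition.

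**The concern.** The hypothesis has two parts, ES better than UI and CELC better than UI. One-way ANOVA and Kruskal-Wallis refer the data to a distribution in which all three arms are alike, and they reject for any departure from it: CELC alone better, ES alone worse, both enhanced arms worse, or ES and CELC differing from each other with UI in between. For four of the five RE-AIM domains, the analysis as written gives one p-value per indicator, and that p-value tests neither superiority claim.

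What is at stake is the decision the trial is meant to inform: whether supervision adds enough to usual implementation, and whether CELC, which contains all of ES plus the learning collaborative, does. That decision needs each arm's own comparison with UI. The point is separate from whether the test allows for clustering. It would remain with a correctly sized cluster-level test.

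**Working it through.** **1. Inputs**

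- Eta-squared 0.025, ICC 0.2, 10 providers per site, 36 sites, 360 providers, target power 80% (Power analysis).
- 12 CHSs and 120 providers per arm (6 per arm in each of two provinces; Study site eligibility and recruitment).
- Two-sided alpha 0.05. The article states this for the client calculation ("power calculations assume near-normal outcomes with a two-sided Type I error of 0.05"). It is assumed here for providers.

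**2. The plan's own figure**

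- f² = 0.025 / 0.975 = 0.02564, so f = 0.160.
- Ignoring clustering, the noncentrality is 360 × 0.02564 = 9.23. With 2 and 357 df the power is 77.8%, slightly under the stated 80%.
- Design effect = 1 + (10 − 1) × 0.2 = 2.8, so the noncentrality is 9.23 / 2.8 = 3.30. With 2 and 33 df the power is 32.3%.

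The drop from 77.8% to 32.3% is a separate matter. Both values are carried forward so that the present point does not depend on it.

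**3. Same eta-squared, different truths**

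If one arm differs from the other two by d, then f² = (2/9)d², so d = √(4.5 × 0.02564) = 0.340 provider SD. The SD of a CHS mean is √(0.2 + 0.8/10) = 0.529 provider SD, so d is 0.64 CHS-mean SD.

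Simulation with 120 independent observations per arm and 200,000 runs. A superiority result is a contrast with UI significant at two-sided 5% in the arm's favour.

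| Truth | Omnibus rejects | ES shown superior | CELC shown superior |
|---|---|---|---|
| Only CELC better | 77.7% | 2.5% | 74.6% |
| Only ES worse | 77.7% | 0% | 2.4% |
| Both better, equally | 78.0% | 74.8% | 74.8% |
| Both worse, equally | 77.7% | 0% | 0% |

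The omnibus column is constant, because the test responds only to the spread of the three means. The four rows have opposite implications for the hypothesis, and only the contrasts separate them. At cluster level (12 CHSs per arm, 2 and 33 df) the omnibus rejection rate is again the same in every row, about 32%.

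**4. Larger, illustrative effects**

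Cluster-level simulation with a correctly sized test and effects in CHS-mean SDs:

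| Truth (UI, ES, CELC) | Omnibus rejects |
|---|---|
| 0, 0, 0 | 5.0% |
| 0, 0, +1.0 | 67–68% |
| 0, −1.0, 0 | 67–68% |
| 0, 0, +1.2 | 83–84% |
| 0, 0, −1.2 | 83–84% |

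At (0, 0, +1.2), ES minus UI is not significant in favour of ES in about 97% of the rejections. If contrasts are tested only after a significant omnibus test, ES is wrongly claimed superior in about 2.5% of trials and CELC is rightly claimed superior in about 77%.

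These effects exceed the plan's. For a shift of 1.0, f² = (2/9) × 0.28 = 0.0622, so eta-squared = 0.0622 / 1.0622 = 0.059. For 1.2 it is 0.082. These are 2.3 and 3.3 times 0.025.

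**The case against.** **The omnibus test matches the aim as worded.** Aim 1 and the Study design section speak of comparing three strategies, and the power calculation is omnibus too (eta-squared for providers, a 4-df chi-square for clients). The directional sentence stands in the Abstract's Discussion and is not presented as a decision rule. This has some force. It is nevertheless the only hypothesis the article states for implementation, and the article does specify a UI reference for improvement and remission.

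**Follow-up contrasts belong in the SAP.** Their absence from a journal article is indeed no finding. The point is narrower: the article names a test for these domains, and that test answers a different question from the stated hypothesis.

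**Stronger readings that the documents do not support.**

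- A reader might infer that none of the RE-AIM primary outcome is compared with UI. That is wrong, because Effectiveness is one of the five domains and has the UI-reference model.
- A reader might set rejection rates of 67–84% against a nominal 5% and call the error rate inflated. Those rates are the power of a correctly sized test when the arms truly differ, at effects well above the planned one. At the planned effect the cluster-level rate is about 32%.
- A reader might infer that harm would be reported as benefit. No passage says that a significant omnibus result will be read as superiority, and arm means or medians are to be shown, so the direction would be visible. Visible means do not, however, test which arm differs from UI.

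**Some contrasts may not be available.** Table 1 takes Adherence and Quality from supervision ratings, and structured supervision is described for ES and CELC but not for UI. This stands, and it limits the fix.

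**Conclusion.** The concern holds for Reach, Adoption, Implementation Quality and Maintenance. For these domains the article names only an omnibus test, which cannot show whether ES or CELC is superior to UI. At the plan's eta-squared of 0.025 it rejects in about 78% of trials ignoring clustering, and in about 32% at cluster level, equally so whether one arm is better, one is worse, or both enhanced arms are worse. The mismatch itself follows from the wording and needs no numerical assumption. The percentages rest on normal outcomes, equal arms, two-sided 5%, and ICC 0.2 with 10 providers per CHS for the cluster-level figures. It is a correctable mismatch between test and hypothesis, not a loss of type I error control, and it does not extend to the Effectiveness model.

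**What to change.** In the RE-AIM outcomes section:

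- Base conclusions for the four domains on two pre-specified contrasts, ES minus UI and CELC minus UI, each with a confidence interval and a stated direction of benefit.
- Take them from a cluster-adjusted model with UI as reference, as the Client outcomes section already does for improvement and remission.
- For supervision-rated indicators, specify these contrasts only where UI data are collected.
- Keep the three-arm test, in a cluster-adjusted form, at most as the gate of a closed test: if it is significant at 5%, test each contrast at two-sided 5%. With three arms this controls the family-wise error within an indicator.
- Claim superiority only for an arm whose own contrast is significant in its favour.

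The cost is a few sentences of analysis wording and no new data. A specific claim has somewhat less power than a claim of some difference: with CELC at +1.2 CHS-mean SD and ES equal to UI, about 77% against about 83%. At the plan's eta-squared with one arm differing, ignoring clustering, a single contrast tested at two-sided 5% has 74.9% power, against 77.8% for the omnibus test.

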#### Provider selection

Based on power considerations, we will recruit 10 providers from each CHS and 360 across the study, including five primary care providers (usually physician assistants or nurses) from the CHS and five (usually VHWs) working with the CHS, totaling 180 CHS providers and 180 non-CHS staff. Providers will be recruited post-enrollment but pre-CHS randomization at each CHS.

We will use a repeated measure design to conduct online self-reported surveys with CHS and non-CHS providers at baseline (before the workshop, during the study enrollment meeting), 6-, 12-, and 24-month follow-up. All follow-up surveys will be distributed and collected by the research coordinator within a one-week period of each data collection time point. The survey will assess the following categories: socio-demographic characteristics (e.g., year of birth, gender, education, number of years working in health system), MH training, depression care attitude scale using the adapted Evidence-Based Practice Attitude Scale (EBPAS) [50], working environment using the Implementation Climate Scale (ICS) [51], CHS head’s leadership using the Implementation Leadership Scale (ILS) [52], depression care activities (e.g., frequency of depression screening and depression treatment offered) and skills, depression stigma [53] and depression knowledge quiz including 20 multiple-choices questions which covers all training topics.

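### For provider-survey outcomes with a baseline, the only arm test named does not use that baseline, which forgoes precision and some protection against chance imbalance but causes no bias

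*Protocol article*

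**What the plan says.** Under Provider selection, the protocol article describes the provider data as longitudinal: "We will use a repeated measure design to conduct online self-reported surveys with CHS and non-CHS providers at baseline". The timing in full is "before the workshop, during the study enrollment meeting), 6-, 12-, and 24-month follow-up". The same section states: "Providers will be recruited post-enrollment but pre-CHS randomization at each CHS". Read together, these put the baseline survey ahead of allocation. Its content includes "depression care activities (e.g., frequency of depression screening and depression treatment offered) and skills", as well as attitude, stigma and knowledge measures.

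Under Study design, provider adoption and implementation quality are what the study primarily tests. Table 1 takes Adoption from the provider survey. Under Power analysis: "Our primary outcome analyses focus on the 12-month timepoint".

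Under RE-AIM outcomes, the one arm comparison given is: "Independent ANOVA and/or Kruskal-Wallis test will be applied to assess differences stratified by intervention arms". The only regression model in the article is the generalized linear mixed model under Client outcomes, which is for the binary client endpoints. No section gives a baseline covariate, a change score or a longitudinal model for provider outcomes.

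**The concern.** The design collects each provider's own baseline before allocation, but the named test takes one value per provider, compares three independent groups and leaves that baseline unused. Kruskal-Wallis cannot take a covariate at all. The article is not silent here, so this is more than a detail left to an analysis plan: the method it names does not match the repeated-measures design that it describes in the next section.

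Adoption is one of the two outcomes the study mainly tests, and there are only 12 CHSs per arm. With few clusters and an ICC of 0.2, arms can differ by chance at baseline, and an unadjusted 12-month contrast contains whatever part of that difference persists. Precision that the baseline survey could supply is also left unused.

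This is separate from whether the test allows for CHS clustering. Running the ANOVA on CHS means would deal with clustering and still leave baseline unused.

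**Working it through.** **Inputs from the article**
- Power analysis: "small eta-squared effect size of 0.025", "expected intra-class correlation coefficient (ICC) of 0.2", 10 providers per site, 360 providers in 36 sites, stated power 80%.
- Study site eligibility and recruitment: 6 CHSs per arm in each of two provinces, so 12 per arm.
- Two-sided alpha 0.05. This is stated for the client outcome and assumed here for providers.

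**Assumption.** The correlation between baseline and 12-month value is not given, so a range is shown: r within CHSs and rc between CHS means.

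**1. The plan's own figure.** f² = 0.025/0.975 = 0.0256. With 360 independent providers the noncentrality is 360 × 0.0256 = 9.23 on F(2, 357), and power is 77.8%. This is near the stated 80% but does not reproduce it, and it ignores the ICC.

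**2. Follow-up only, clustering respected.** Variance of a CHS mean = 0.2 + 0.8/10 = 0.28. Noncentrality = 36 × 0.0256/0.28 = 3.30 on F(2, 33). Power = 32%.

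**3. Baseline as covariate, clustering respected.** Variance = 0.2(1 − rc²) + 0.08(1 − r²), tested on F(2, 32).

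| rc (between) | r (within) | Variance | Noncentrality | Power |
|---|---|---|---|---|
| not used | not used | 0.280 | 3.30 | 32% |
| 0.3 | 0.3 | 0.255 | 3.62 | 35% |
| 0.5 | 0.5 | 0.210 | 4.40 | 42% |
| 0.7 | 0.7 | 0.143 | 6.46 | 58% |
| 0 | 0.5 | 0.260 | 3.55 | 34% |

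With equal correlations at both levels the variance falls by r², that is 9%, 25% and 49%. In the last row baseline carries no information between CHSs, and the gain is about 2 points. A simulation of CHS means (3,000 runs per setting) gave 0.31–0.32 unadjusted and 0.33, 0.40 and 0.56 adjusted. Rejection under the null was 0.042–0.050 for both analyses.

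**4. Sensitivity to the ICC, at a correlation of 0.5.** At an ICC of 0.05, power goes from 57% to 70%. With observations treated as independent, it goes from 78% to 89%.

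**5. Chance imbalance.** Ignoring matching, the standard error of a baseline difference between two arms is √(2 × 0.28/12) = 0.22 SD. At a correlation of 0.5, a one-standard-error imbalance moves an unadjusted contrast by 0.5 × 0.22 = 0.11 SD. This is an upper figure: if matching removed all variation between CHSs, the standard error would be √(2 × 0.08/12) = 0.12 SD.

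**The case against.** The strongest reply is that nothing here is an error. Under randomisation an unadjusted follow-up comparison is unbiased, and its standard error already allows for chance imbalance; the null rejection rates above agree. The stated power never counted on baseline adjustment. All of this stands. A reader might infer that the planned comparison is biased, or that power promised by the design is lost, and the documents support neither. What is given up is a gain that was available.

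Second, sites are matched within district before randomisation, with 3 high and 3 low performers per arm in each province. A reader might infer that protection against imbalance is absent; it is not. Matching acts on the CHS component, which supplies 0.20 of the 0.28 variance. It does not act on providers' own practice, knowledge, attitude or stigma scores beyond what site characteristics predict.

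Third, the covariate may be weakest for Adoption. Table 1 lists only follow-up times for it, the cost-effectiveness section defines it among trained providers, and the baseline comes before training. Practices near zero at baseline are plausible, and the gain would then be small. This stands for Adoption but need not apply to knowledge, attitude and stigma.

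Fourth, the sentence also covers indicators without a pre-randomisation baseline (Reach, supervisor ratings, completion, dropout), where an independent-groups comparison is natural. And knowledge, attitude and stigma are not Table 1 indicators, so the named test may not have been meant for them. Both are accepted, and the point is limited accordingly.

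Fifth, the same sentence has a larger, separate fault: the test as written has no CHS term. In simulation at an ICC of 0.2, a provider-level ANOVA that ignores sites rejects a true null about 35% of the time. That is why the figures above respect clustering in both analyses.

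**Conclusion.** The point holds in a limited form. For provider-survey outcomes that have a baseline, the article names an arm test that does not use it, although its design collects it before allocation. The consequence is precision forgone and weaker protection against chance provider-level imbalance.

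The size is uncertain because it rests on a correlation the article does not give. With the plan's effect size, an ICC of 0.2 and clustering respected, the gain is about 3, 9 or 25 points of power over 32% at correlations of 0.3, 0.5 and 0.7. It is about 2 points if baseline is uninformative between CHSs, and probably small for practices near zero before training. The 9-point figure should not be read as the expected gain for Adoption. Even at a correlation of 0.7, power on these inputs is 58%, so baseline adjustment alone does not bring it to the stated 80%.

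This is a worthwhile, low-cost improvement to a stated method. It does not threaten the validity of the trial.

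**What to change.** For provider-survey outcomes with a baseline, replace the independent ANOVA/Kruskal-Wallis under RE-AIM outcomes with a mixed model for the follow-up values. Fixed effects: arm, visit, arm-by-visit, the provider's baseline value of the same item, and the matching factors (province, district/performance stratum). Random effects: provider and CHS. Use a link suited to the item where it is a count or binary. Name the 12-month arm contrast as the primary provider result.

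For indicators without a baseline (Reach, supervisor ratings, completion, dropout), keep ANOVA/Kruskal-Wallis on CHS-level summaries.

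Reconcile the assessment times in the same edit: Table 1 lists Adoption at 36 months, while the survey schedule under Provider selection ends at 24 months. The visits in the model depend on which is meant.

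Cost: wording only, settled before arm comparisons are seen. The baseline survey is already part of the design, so no sites, visits or data are added. The model is somewhat larger than a one-way test, and it will gain little for items near zero at baseline.
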